### Recruitment {15}

Participants will be recruited in ten hospitals across China. We will conduct recruitment in outpatient clinic, inpatient department, and emergency department. Participants will be recruited through four mechanisms: (1) suitable patients encountered by the investigators in their clinical work; (2) putting up posters in hospitals; (3) releasing relevant information through WeChat official account; (4) investigators regularly identify suitable participants in the hospitals’ medical imaging system.

## Assignment of interventions: allocation

### Sequence generation {16a}

Enrolled participants will be randomly assigned to the intervention group or the control group, allocated by the Interactive Web Response System (IWRS) with a ratio of 1:1. The randomization sequence will be generated in fixed block sizes and stratified by center. After informed consent, the investigators will log into IWRS to acquire a unique identification code and random number of each participant for participant identification and treatment assignment.

### Concealment mechanism {16b}

Allocation is concealed and will not be revealed to neither the participants nor the investigators upon randomization. Participants will be randomized by the Interactive Web Response System (IWRS), which is an online, central randomization service. IWRS will ensure the allocation concealment. It will only offer a random number to the investigator. Neither the investigators nor the participants will know from random numbers whether they represent the intervention group or the control group.

### Implementation {16c}

After signing the informed consent forms, the investigators will use the Interactive Web Response System (IWRS) to allocate the participant to one of the study arms.

## Assignment of interventions: Blinding

### Who will be blinded {17a}

Participants and investigators will be blinded. Blinding is ensured by using the double-blind technique. The lumbrokinase and the placebo of lumbrokinase will be identical in size, color, and smell. Each medication bottle will be labelled with a unique kit identity number, which corresponds to the random number obtained by IWRS. The number will be used to assign treatment without treatment allocation information. Outcome assessors or data analysts will also be blinded to treatment allocation. An employee outside the research team will export the data from the electronic CRF system so that outcome assessors or data analysts could analyze data without having access to the information about the allocation.

### Procedure for unblinding if needed {17b}

When a serious adverse event occurs, and it is difficult to judge the relationship between the event with interventions or overdose or serious drug interaction with the combined use of drugs, the investigator could reveal a participant’s allocated intervention in the IWRS.

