### Outcomes {12}

The primary outcome is the Modified Rankin Scale (mRS) score.

The secondary outcomes are National Institutes of Health Stroke Scale (NIHSS) score, Activity of Daily Living (ADL) Scale score (Barthel index), coagulation function: prothrombin time (PT), activated partial thromboplastin time (APTT), serum fibrinogen (FIB) concentration, and serum hypersensitive C-reactive protein (hs-CRP).

The safety outcomes are liver function and kidney function: alanine aminotransferase (ALT), aspartate aminotransferase (AST), total bilirubin (TBil), blood urea nitrogen (BUN), serum creatinine (Scr), and urine protein (R-PRO), as well as serum fibrinogen (FIB), occurrence of adverse events (AEs) and serious adverse events (SAEs), and occurrence of bleeding events. Adherence of participants will also be assessed.

The exploratory outcomes include fasting lipid panel: total cholesterol (TC), triglyceride (TG), high-density lipoprotein (HDL), low-density lipoprotein (LDL), and recurrence rate (incidence of ischemic stroke events), occurrence of cardiovascular and cerebrovascular events, and mortality rate. A study schedule and evaluation of outcomes are provided in Table 1.

The five elements of the primary outcome and secondary outcomes are specified in Table 2: the domain, specific measurement, specific metric, method of aggregation, and time point.

**Table 2 Tab2:** Five elements of outcomes

	Domain	Specific measurement	Specific metric	Method of aggregation	Time point
Primary outcome	The Modified Rankin Scale (mRS) score	The Modified Rankin Scale (mRS) score	Change from baseline to 14, 28, 60, 90, and 180 days	Proportional-odds logistic-regression model	Baseline, 14, 28, 60, 90, and 180 days
Secondary outcome	National Institutes of Health Stroke Scale (NIHSS) score	National Institutes of Health Stroke Scale (NIHSS) score	Change from screening period to 14, 28, 60, and 90 days	Repeated-measures analysis model	Screening period, 14, 28, 60, and 90 days
	Activity of Daily Living (ADL) Scale score (Barthel index)	Activity of Daily Living (ADL) Scale score (Barthel index)	Change from baseline to 90 and 180 days	Repeated-measures analysis model	Baseline, 90 and 180 days
	Prothrombin time (PT)	Prothrombin time (PT)	Change from baseline to 14, 28, 60, and 90 days	Repeated-measures analysis model	Baseline, 14, 28, 60, and 90 days

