## Statistical methods

### Statistical methods for primary and secondary outcomes {20a}

The primary outcome will be analyzed by fitting a proportional-odds logistic-regression model to calculate the common odds ratio as a measure of the likelihood that the treatment group will lead to lower mRS scores than the control group (shift analysis).

For secondary outcomes, categorical variables will be compared with chi-square test or Fisher exact test. Longitudinal continuous variables will be analyzed by fitting a repeated-measures analysis model. Additionally, adverse events, serious adverse events, and laboratory abnormalities will also be compared using the chi-square test or Fisher exact test as appropriate.

All analyses will be performed in the intention-to-treat population using SAS version 9.4 (SAS Institute Inc). *P* values of less than 0.05 will be considered statistical significance, and all tests will be two-sided. No adjustments will be made for multiple comparisons.

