### Adverse event reporting and harms {22}

All adverse events reported by the participants or observed by the investigators will be recorded. Adverse events will begin to be collected after the participant has provided consent and enrolled in the trial. An adverse event is recorded at any time. When an adverse event occurs, it is recorded immediately. If a participant experiences an adverse event after the informed consent document is signed (entry) but the participant has not started to receive any study intervention, the event will be reported as not related to the study drug [13]. All adverse events occurring after entry into the trial and until the 90th day will be recorded. An adverse event that meets the criteria for a serious adverse event (SAE) between study enrollment and the 90th day will be reported to both the ethics committee of the hospital, and the Ethics Committee of Dongzhimen Hospital, Beijing University of Chinese Medicine as an SAE. A serious adverse event for this trial is any untoward medical occurrence that is believed by the investigators to be causally related to study drug and results in any of the following: after receiving the study drug, the participants need to be hospitalized, need to prolong the length of hospital stay, become disabled, be life threatened or dead, have congenital malformation, and other events. Investigators will evaluate the causal relationship between adverse events and study drugs.

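### The unblinding rule and the SAE definition are circular, and together they let knowledge of the arm decide whether a doubtful event counts as an SAE

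*Protocol article*

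**What the plan says.** Four parts of the protocol article bear on this.

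- **Who will be blinded {17a}:** "Participants and investigators will be blinded". The same section adds that outcome assessors or data analysts are blinded too.
- **Procedure for unblinding if needed {17b}:** the code may be opened "When a serious adverse event occurs, and it is difficult to judge the relationship between the event with interventions" or certain other circumstances. The person who may open it is the investigator: "serious drug interaction with the combined use of drugs, the investigator could reveal a participant"'s allocation in the IWRS.
- **Adverse event reporting and harms {22}:** an SAE is "any untoward medical occurrence that is believed by the investigators to be causally related to study drug" and that has one of a list of serious consequences. The judgement is given to the same role: "Investigators will evaluate the causal relationship between adverse events and study drugs".
- **Outcomes {12} and Statistical methods {20a}:** the safety outcomes include "occurrence of adverse events (AEs) and serious adverse events (SAEs), and occurrence of bleeding events". In the analysis, "adverse events, serious adverse events, and laboratory abnormalities will also be compared using the chi-square test or Fisher exact test as appropriate", and P "values of less than 0.05 will be considered statistical significance, and all tests will be two-sided".

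**The concern.** The SAE definition in {22} has two conditions: a serious consequence and the investigator's belief in a causal link. The second is a judgement, and {17b} allows the allocation to be revealed precisely when that judgement is hard. One role may therefore open the code, decide causality with the arm known, and so decide whether the event enters a count that is tested between arms.

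The information gained is not symmetric. Learning that a participant took placebo rules out lumbrokinase as the cause; learning that a participant took lumbrokinase does not. The likely tendency is for doubtful events to stay in the SAE count on lumbrokinase and leave it on placebo. An investigator who favours the drug could push the other way. In either direction, the comparison loses the protection of blinding in the cases where it matters most.

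**Working it through.** **Reading the two sections together**

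1. Suppose SAE in {17b} carries the meaning given in {22}. The investigators must then already believe the event to be drug-related. Yet the ground for opening the code is that the relationship is hard to judge. The trigger undercuts its own precondition.
2. Suppose instead that SAE in {17b} means any event with a serious consequence. The event is then not yet an SAE under {22}. The code is opened, causality is judged, and that judgement settles whether the event becomes an SAE. Knowledge of the arm enters the classification.
3. Under either reading, the two sections do not say which causality judgement, before or after the break, decides the count.

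**Illustration of size**

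The plan gives no figure to reproduce on this point. From the documents: n = 110 per arm (Sample size {14}) and a two-sided 0.05 level ({20a}). Everything else is assumed, with at most one event counted per participant:

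- r = true serious-event rate, equal in both arms: 10%, then 20%
- q = proportion attributed to study drug when judged blind: 50%
- u = share of serious events unblinded: 0, 25% or 50%
- q_L, q_P = proportion attributed once unblinded: 70% on lumbrokinase, 10% on placebo

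Expected SAEs in an arm = n × r × [(1 − u) × q + u × q_arm].

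With r = 10%, n × r = 110 × 0.10 = 11 serious events per arm:

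- u = 0: 11 × 0.50 = 5.5 in each arm
- u = 25%: lumbrokinase 11 × (0.375 + 0.175) = 6.05, about 6.1; placebo 11 × (0.375 + 0.025) = 4.4
- u = 50%: lumbrokinase 11 × (0.25 + 0.35) = 6.6; placebo 11 × (0.25 + 0.05) = 3.3

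The spurious difference is n × r × u × (q_L − q_P) = 11 × u × 0.60 = 6.6u. It is proportional to the share of events unblinded and vanishes as u goes to zero. At u = 10% it is 0.66 of a participant.

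Exact binomial enumeration of both tests, with no true difference between the arms, gives these false-positive rates:

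| r | u | Expected SAEs, lumbrokinase v placebo | Chi-square | Fisher |
|---|---|---|---|---|
| 10% | 0 | 5.5 v 5.5 | 4.5% | 2.3% |
| 10% | 25% | 6.1 v 4.4 | 7.3% | 4.0% |
| 10% | 50% | 6.6 v 3.3 | 17.1% | 10.7% |
| 20% | 0 | 11.0 v 11.0 | 5.3% | 3.0% |
| 20% | 50% | 13.2 v 6.6 | 35.5% | 26.6% |

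**Effect of defining SAE by seriousness alone**

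At r = 10%, all 11 serious events count in each arm, whatever is known about the allocation. That is a 10% count rate per arm, the same as the fourth row of the table (20% × 50%). The false-positive rates are therefore 5.3% (chi-square) and 3.0% (Fisher), for any u.

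**The case against.** Several limits on the concern are fair.

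- **The rule is permissive and narrow.** The investigator could open the code, for one participant, in a hard case. Nothing says how often this would happen. This stands: the count can become arm-dependent, but not that it will.
- **If the {22} definition is read into {17b}, the event is already in the count before the code is opened.** This is a possible reading, but it makes the trigger contradict itself, and neither section prevents a doubtful attribution from being revised afterwards. It supports reconciling the sections rather than leaving them.
- **Placebo participants also take aspirin.** Study drug is not defined as excluding it, so attribution on placebo need not fall to zero. This stands and limits the size.
- **The safety answer does not rest on SAEs alone.** All adverse events are recorded whatever their cause, and bleeding events and mortality are listed separately. This stands; it softens the consequence but does not repair the SAE comparison.

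A reader might also infer two stronger points that the documents do not support.

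- **A spurious excess of about five participants.** This follows only if every serious event is unblinded and attribution is 50% v 0%: 11 × 0.5 = 5.5 v 0. That is a ceiling built on extreme assumptions.
- **Later mRS, NIHSS or Barthel ratings are made unblinded.** An investigator who opens the code does know that participant's arm. But no section says that this person does the later ratings, and {17a} states that outcome assessors are blinded. The question is open only because Plans for assessment {18a} describes those assessors as analysing data after database lock and no visit rater is named. In a condensed article that is an unknown, not an error.

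**Conclusion.** The point holds as a flaw in the stated rules. Sections {17b} and {22} are circular, and together they permit knowledge of the arm to decide whether a doubtful event is an SAE, which is an outcome compared between arms.

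The size cannot be known from the documents. Under the stated assumptions at a 10% event rate, the expected spurious difference is 6.05 − 4.4 = 1.65 participants with a quarter of events unblinded and 6.6 − 3.3 = 3.3 with half unblinded. With a quarter unblinded, Fisher's test still stays below 5%. The figures rest wholly on the assumed event rate, attribution shift and share of codes broken; with few breaks the effect is negligible. The change is worth making because it is cheap and removes the dependence whatever those values are. Loss of blinding in later outcome ratings should be recorded only as an open risk.

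**What to change.** 1. Reconcile {17b} and {22}, so that the ground for opening the code and the meaning of SAE no longer depend on each other. Which grounds for a code break are kept is for the sponsor and investigators to settle.
2. In {22}, define SAE by seriousness alone. The comparison in {20a} then counts all serious events regardless of causality.
3. Require the causality judgement to be recorded before any code break, and use only that blinded judgement in any analysis of related events.
4. Report code breaks by arm.

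The cost is protocol wording and one CRF field. Some causality entries will read as cannot be judged; with seriousness as the definition, those events still count. SAE counts will rise in both arms (from 5.5 to 11 per arm in the example), and with them the reports to the ethics committees. Trial status gives 46 of 220 recruited on 29 November 2021, so at that date an amendment would have covered the remaining 174 from entry. Serious events among the first 46 can be reclassified, since all adverse events to day 90 are recorded.

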## Data collection and management

### Plans for assessment and collection of outcomes {18a}

Investigators will be trained prior to recruiting participants and data will be managed as stated in Standard Operating Procedures (SOPs). Accuracy, reliability, and reference values of laboratory tests at each hospital will be unified prior to the start of this trial. Data from case report form (CRF) will be entered and stored in the electronic CRF system. A specialized quality monitor will regularly review CRFs and inspect the data. Monitoring results will be presented to the investigator-in-charge in each hospital, and the investigator-in-charge at each hospital is responsible for the accuracy, completeness, and timeliness of the recorded data. After all participants complete the 180-day visit and the data management team confirms all data have no issue, the database will be locked and then the outcome assessors or data analysts will begin to analyze the data under blinding. When data analysis is completed, the blinding will be open.

### Plans to promote participant retention and complete follow-up {18b}

The participants will receive extensive information about the study setup and requirements during the recruitment. The importance of completion of the follow-up will be stressed. Participants are allowed to stop at any time during the study and are not obliged to give a reason to discontinue. Throughout the follow-up period, the investigators will contact participants for completion of their follow-up.

### Data management {19}

In this trial, all data will be filled in the original case report form. Then they will be entered in the electronic case report form. Original case report forms will be kept on file at the participating site. Data integrity of the electronic case report form will be enforced through a variety of mechanisms, such as referential data rules, valid values, range checks, and consistency checks against data already stored in the database. Modifications to data entered in the electronic case report form will be documented through either the data change system or an inquiry system. An independent data monitoring committee (DMC) will periodically monitor the data entry of each hospital. The executive committee will publicize the enrollment of all hospitals on a weekly basis.

### Confidentiality {27}

Research data will be stored using a participant’s number for each participant. The key to the participant’s number will only be available to the research team during the study. No participant identification details will be reported in publications.

### Plans for collection, laboratory evaluation, and storage of biological specimens for genetic or molecular analysis in this trial/future use {33}

This trial will not collect biological specimens.

## Statistical methods

### Statistical methods for primary and secondary outcomes {20a}

The primary outcome will be analyzed by fitting a proportional-odds logistic-regression model to calculate the common odds ratio as a measure of the likelihood that the treatment group will lead to lower mRS scores than the control group (shift analysis).

For secondary outcomes, categorical variables will be compared with chi-square test or Fisher exact test. Longitudinal continuous variables will be analyzed by fitting a repeated-measures analysis model. Additionally, adverse events, serious adverse events, and laboratory abnormalities will also be compared using the chi-square test or Fisher exact test as appropriate.

All analyses will be performed in the intention-to-treat population using SAS version 9.4 (SAS Institute Inc). *P* values of less than 0.05 will be considered statistical significance, and all tests will be two-sided. No adjustments will be made for multiple comparisons.

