### Trial design {8}

In this prospective, multicenter, randomized, double-blind, placebo-controlled clinical trial, lumbrokinase plus aspirin is compared to aspirin alone. We plan to enroll 220 participants with first time diagnosis of AIS. The participant allocation ratio is 1:1. Participants will be treated for the first 90 days. Then, all participants will be treated with aspirin only and followed up for another 90 days (180-day follow-up). A flowchart of the study is shown in Fig. 2. Central ethical approval of LUCENT has been confirmed by the Ethics Committee of Dongzhimen Hospital, Beijing University of Chinese Medicine (No.DZMEC-KY-2019-202). This trial will be conducted in adherence to the Declaration of Helsinki. Informed consent will be obtained from all participants or their legal representative, in writing, before inclusion in the trial. The trial has been registered in the Chinese Clinical Trial Registry (ChiCTR2000032952).

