**Coagulation function**							
PT		X	X	X	X	X	
APTT		X	X	X	X	X	
FIB		X	X	X	X	X	
hs-CRP		X				X	
Homocysteine	X						
ECG	X					X	
MRI of brain	X					X	
ADL scale (BI)		X				X	X
NIHSS	X		X	X	X	X	
mRS before stroke	X						
mRS		X	X	X	X	X	X
Recurrence rate			X	X	X	X	X
Cardiovascular and cerebrovascular events			X	X	X	X	X
Bleeding event			X	X	X	X	
Mortality rate			X	X	X	X	X
AE and SAE		X	X	X	X	X	
Combined use of drugs		X	X	X	X	X	
Adherence evaluation			X	X	X	X	

Abbreviations: *TIA*, transient ischaemic attack; *RBC*, erythrocyte count; *WBC*, leukocyte count; *PLT*, blood platelet; *Hb*, hemoglobin; *PCV*, packed cell volume; *U-LEU*, urine leukocyte; *U-BLD*, urine latent blood; *R-PRO*, urine protein; *U-Ket*, urine ketone bodies; *OB*, fecal occult blood; *ALT*, alanine aminotransferase; *AST*, aspartate aminotransferase; *TBil*, total bilirubin; *BUN*, blood urea nitrogen; *Scr*, serum creatinine; *TC*, total cholesterol; *TG*, triglyceride; *HDL*, high-density lipoprotein; *LDL*, low-density lipoprotein; *PT*, prothrombin time; *APTT*, activated partial thromboplastin time; *FIB*, fibrinogen; *hs-CRP*, hypersensitive C-reactive protein; *ECG*, electrocardiogram; *MRI*, magnetic resonance imaging; *ADL*, activity of daily living; *BI*, Barthel Index; *NIHSS*, National Institutes of Health Stroke Scale; *mRS*, Modified Rankin Scale; *AE*, adverse event; *SAE*, serious adverse event

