### Sample size {14}

A sample size of 173 participants was calculated to provide 80% power to detect a common odds ratio (indicating the odds of improvement of 1 point on the mRS) of 6.02 in the distribution of scores on the mRS at 90 days between the treatment and control groups with a two-sided significance level of 0.05, assuming a similar between-group distribution of the mRS as in a recent AIS trial [11]. Taking into account of possible protocol violations and dropouts, we intend to enroll 220 participants (110 per group).

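### The primary mRS model as stated names neither the stratifying centre nor the baseline predictors collected; adjusting for them would gain efficiency, though the analysis as written is valid

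*Protocol article*

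**What the plan says.** On the primary analysis, the section Statistical methods for primary and secondary outcomes {20a} states: "The primary outcome will be analyzed by fitting a proportional-odds logistic-regression model to calculate the common odds ratio". The contrast described is treatment against control. No covariate is listed, and the model is not called unadjusted. Table 2, under Outcomes {12}, repeats the model class and gives the primary metric as "Change from baseline to 14, 28, 60, 90, and 180 days". For longitudinal secondary outcomes, {20a} names a repeated-measures model without listing its terms.

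On the design, Sequence generation {16a} states: "The randomization sequence will be generated in fixed block sizes and stratified by center". Recruitment {15} gives the number of strata: "Participants will be recruited in ten hospitals across China".

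On baseline data, Eligibility criteria {10} admit NIHSS 6 to 14, age 35 to 85 and pre-stroke mRS 0 to 2. Table 1 schedules NIHSS, demographic data and "mRS before stroke" at screening.

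Sample size {14} sets the calculation at day 90: "A sample size of 173 participants was calculated to provide 80% power", for a common odds ratio of 6.02.

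**The concern.** The design uses centre to balance the arms, but the stated analysis does not carry centre through. When outcomes differ between centres, a model that ignores the stratifier tends to overstate the standard error.

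Initial severity, age and prior disability are natural candidates to explain variation in mRS after stroke. Here they are recorded before treatment, so using them needs no new data. Left out, they remain in the residual noise, and a chance imbalance in NIHSS or age stays in the estimate. The change-from-baseline metric in Table 2 does not replace this: even if a change score were analysed, it would not account for NIHSS, age, pre-stroke mRS or centre.

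Efficiency matters in this trial. Trial status reports 46 participants from September 2020 to 29 November 2021, about 3 a month over 15 months. The remaining 174 by August 2022 would need about 174/9 = 19 a month. If recruitment falls short, adjustment is a way to recover some precision.

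**Working it through.** **Step 1: the plan's own figure.** This decides the effect size at which a gain should be judged. Inputs from the protocol: "The participant allocation ratio is 1:1", "two-sided significance level of 0.05", 80% power, odds ratio 6.02, total 173. The mRS distribution is not given (it comes from a cited trial), so several were assumed. Whitehead's formula for the total sample size is

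N = 12(z_α + z_β)² / [ln(OR)² (1 − Σp̄³)], where p̄ are the category proportions averaged over the arms.

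Here 12(1.960 + 0.842)² ≈ 94.2 and ln(6.02)² = 1.795² ≈ 3.22, so N ≈ 29.2/(1 − Σp̄³).

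| Assumed control distribution | 1 − Σp̄³ | N at OR 6.02 | OR giving N = 173 |
|---|---|---|---|
| Uniform, seven levels | 0.956 | 30.6 | 2.11 |
| Spread (8/17/18/19/22/8/8%) | 0.965 | 30.3 | 2.12 |
| Milder (20/30/20/12/10/4/4%) | 0.911 | 32.1 | 2.14 |
| Concentrated (75% in one level) | 0.770 | 38.0 | 2.49 |
| Binary 50/50 | 0.654 | 44.7 | 2.39 |
| Binary 90/10 | 0.167 | 175.3 | 6.10 |

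The 173 is not reproduced except with about 90% of controls in the best category, which is implausible for entry NIHSS 6 to 14. For spread seven-level distributions, 173 patients give 80% power at an odds ratio of about 2.1.

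Power at OR 6.02 and N = 173 is Φ(ln(6.02)·√[173(1 − Σp̄³)/12] − 1.96). For the spread distribution this is Φ(1.795 × 3.73 − 1.96) = Φ(4.74), above 99.9%. The same holds for every row except the last (79.5%). At the stated effect there is therefore nothing visible for adjustment to gain.

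**Step 2: the gain near OR 2.1 to 2.2.** Main simulation: N = 173, the spread distribution above, ten equal centres, blocks of four, marginal odds ratio about 2.18, and one normal prognostic score standing for the baseline covariates together. Each setting had 800 runs, with a Monte Carlo standard error of about 1.4 points or less. The centre standard deviation (log-odds scale) and the share of latent variance explained are assumed; the documents give neither. Centre was fitted as fixed effects. Power, in percent:

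| Variance explained by score | Centre SD | Treatment only | + score | + centre | + both |
|---|---|---|---|---|---|
| 10% | 0.2 | 80.9 | 86.8 | 82.5 | 87.9 |
| 19% | 0.3 | 81.5 | 89.8 | 83.1 | 91.9 |
| 18% | 0.6 | 80.6 | 88.4 | 84.5 | 91.8 |
| 30% | 0.3 | 81.0 | 93.5 | 83.5 | 94.8 |
| 40% | 0.3 | 78.6 | 95.3 | 80.8 | 96.0 |

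For 10% to 30% explained, the score alone adds about 6 to 12.5 points. Centre alone adds about 2 to 4 points across all rows.

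A second simulation (OR 2.2, centre SD 0.3, 400 runs per setting) gave 79.5 to 86.3, 80.3 to 89.8 and 77.3 to 91.8 for 10%, 20% and 30% explained. With no centre effect and 20% explained it gave 81.3 to 88.5. A third gave 76–86% unadjusted against 89–90% adjusted. The smallest gain is about 3 points (86 to 89) and the largest about 14.5 (77.3 to 91.8), hence very roughly 3 to 15.

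**Step 3: validity.** With no treatment effect, 19% explained at centre SD 0.3 and 18% at 0.6 (1,500 runs each, standard error about 0.6 points), the model without covariates rejected in 4.4% and 5.1% of runs. Fixed centre effects gave 5.3% and 5.9% without the score, and 4.9% and 5.7% with it. A separate set of 700 null runs with fixed centre effects gave 6.3% (standard error about 0.9 points).

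**The case against.** The strongest objection is that the article is silent rather than wrong. A reader might infer that the sponsor chose a treatment-only model. The text does not say so: this is a condensed article, any analysis plan is not shown, and covariate lists are often placed there. Stratifying by centre does not contradict a sentence that names no covariates. This stands, and it is why the point is limited to the model as stated.

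The size is also assumption-bound. The documents give no prognostic strength, centre variation or mRS distribution, and the odds ratio of 2.1 to 2.2 replaces the stated 6.02. Entry limits narrow NIHSS and pre-stroke mRS, so the upper end of the variance range may be optimistic. This stands too.

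A further objection is that analysis is planned under blinding (Plans for assessment and collection of outcomes {18a}), which limits choosing between adjusted and unadjusted results. It does so only in part: two fits can be compared by their p-values without knowing which arm is which. Naming the model closes that choice.

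**Conclusion.** The point holds as a matter of efficiency and of fixing the model in advance. The stated primary model names neither the stratification factor nor the predictors already collected, and a better model is available from the same data. With N = 173, an odds ratio of about 2.1 to 2.2 and 10% to 30% of latent variance explained, the gain is very roughly 3 to 15 points of power, nearly all from the baseline covariates. At 6.02 there is no visible gain.

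Two stronger readings should be resisted. A reader might infer that ignoring centre makes the analysis invalid or biased; the simulated type I error of 4.4% to 5.1% does not support that. A reader might also infer that power is given up at no cost in return. Adjustment has a price, and the size of the gain rests on inputs that the documents do not give.

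That 6.02 and 173 do not fit together is a separate matter for the sample-size section.

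**What to change.** In {20a}, specify the primary model as mRS at day 90 (the time point used for the sample size) on treatment, screening NIHSS (continuous), age (continuous) and pre-stroke mRS, with centre as a random intercept or with small centres pooled. Report the unadjusted odds ratio as supportive. In the repeated-measures models for NIHSS, Barthel index, PT, APTT, fibrinogen and hs-CRP, include the baseline value (screening value for NIHSS) and centre. If an analysis plan already specifies this, a cross-reference is enough.

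The cost is one sentence and no new data. There are two downsides:

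- The adjusted odds ratio is conditional on the covariates and lies further from 1 than the marginal one. In the simulations a marginal value of about 2.18 corresponded to conditional values of 2.28 to 2.57 for 10% to 30% explained, so the report must say which is shown.
- Sparse centres need a random effect or pooling rather than a separate fixed effect for each centre. 173/10 is about 17 patients per centre over seven outcome levels, and real centres will be unequal. The 6.3% seen with fixed effects is within about 1.5 standard errors of 5%, so this is a precaution, not a demonstrated inflation.
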